### Duration of the FIT-HIP intervention

The FIT-HIP intervention, integrated in the usual care, will be conducted during the entire period that the participant is admitted to GR. The duration of the inpatient GR is determined for each participant individually, and is therefore variable. On average, the duration of admission to GR for rehabilitation after hip fracture is 6 weeks. During the trial, the following is registered: i) total duration of GR in days, ii) number of therapy sessions during GR, iii) duration of therapy sessions, and iv) (in the intervention group) performance of the individual components of the FIT-HIP intervention; all these elements can be used as confounding variables in the final outcome analyses.

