### Randomisation (and allocation)

Of the 11 post-acute GR units, six will be randomly allocated by computer-generated randomisation to conduct the FIT-HIP intervention and five are allocated to the control group (usual care). Hip fracture patients will be screened for eligibility for the FIT-HIP study on admission to these post-acute GR units. For this trial, each post-acute GR unit will include a maximum of 15 participants (in order of succession in which patients are admitted to GR, eligible, and willing to participate). Participants will receive treatment (usual care, or the addition of FIT-HIP intervention to usual care) according to the randomisation of the post-acute GR unit to which they are admitted.

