#### Secondary outcomes

Table 1 gives an overview of the secondary outcome measures in the effect evaluation. For these outcome measures, at discharge from GR, mean differences between the intervention and control group will be assessed.

**Table 1 Tab1:** Secondary outcome measures in the FIT-HIP trial

Domain	Assessment	Description	Time point(s)
Physical functioning and activity	Barthel index [40]	Activities in daily living. Measures (in)dependence in personal care (eating, dressing, bathing, going to the toilet) and mobility.	BA, DA, FU1, FU2
	Functional ambulation categories [41]	Evaluates ambulation ability, describing the degree of human support the person needs when walking.	BA, DA, FU1, FU2
	10 meter walk test [42, 43]	Assesses walking function/speed.	BA, DA
	Activity restriction due to fear of falling	Assessed in questionnaire, asking if participant has experienced restriction of activity due to the fear of falling.	BA, DA, FU1, FU2
Falls, complications and health care service usage	Falls (and fall-related injury)	Number of fall incidents and medical attention required as a result of the fall. Assessed using monthly fall calendars.	BA, DA, FU1, FU2
	Complications during GR	Number and type of complication occurring during GR. Assessed by elderly care physician (ECP) in monthly calendars.	Until discharge from GR
	Hospital (re)admission	Number of hospital readmissions and days in hospital. Assessed by ECP in monthly calendars during GR and questionnaire at discharge from GR. Assessed by participants using questionnaire in FU.	DA, FU1, FU2
	Mortality		DA, FU1, FU2
	Healthcare consumption after discharge	Number of contacts with health and community services. Assessed by participants using questionnaire in FU.	FU1, FU2
Other outcome characteristics of GR	Duration of admission to GR	Number of days admitted to GR. Assessed by ECP (questionnaire).	DA
	Total amount of therapy in GR	Number of hours of physiotherapy and of contact with ECP. Assessed by physiotherapists in weekly calendars and by ECP in monthly calendars.	Until discharge from GR
	Discharge location	Location of the residence to which participant is discharged after GR. Assessed by ECP (questionnaire).	DA
Health-related quality of life	EuroQol 5D (EQ5D) [44]	The three-level EuroQol 5D (EQ-5D) is a standardised instrument for measuring generic health status. It can be used for calculating quality adjusted life years (QALYs), for the economic evaluation.	BA, DA, FU1, FU2

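### The protocol lets four items that arise during treatment be adjusted for as confounders; used in the effect models, this could bias the intention-to-treat estimate in either direction

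*Protocol article*

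**What the plan says.** The section Duration of the FIT-HIP intervention lists four things to be recorded: "total duration of GR in days", "number of therapy sessions during GR, iii) duration of therapy sessions", and "in the intervention group) performance of the individual components of the FIT-HIP intervention". It closes with the statement that "all these elements can be used as confounding variables in the final outcome analyses".

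Other sections bear on this:

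- Randomisation (and allocation): participants are treated "according to the randomisation of the post-acute GR unit to which they are admitted".
- Secondary outcomes, Table 1: duration of admission ("Number of days admitted to GR. Assessed by ECP (questionnaire") and total amount of therapy ("Number of hours of physiotherapy and of contact with ECP") are outcomes. For the Table 1 measures, "mean differences between the intervention and control group will be assessed".
- Data analyses: multilevel models for continuous outcomes on an intention-to-treat basis, with no covariates named.
- Primary outcome: POMA and FES-I, each as a mean difference between the arms at discharge or at most 3 months after admission.

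**The concern.** A confounder of the arm comparison has to be in place before treatment acts. These four items accrue during the stay, under the treatment that the unit's allocation has already fixed. The first three may themselves be changed by FIT-HIP, and the fourth is a record of FIT-HIP being given.

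Adjusting for such items can distort the arm coefficient in two ways. It removes whatever part of the effect runs through stay or therapy. It also compares patients who reached the same stay or therapy dose by different routes, which brings unmeasured prognosis such as frailty into the comparison.

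At stake is the estimate for both primary outcomes. Because the clause is optional and has no stated limit, the choice to adjust could also be made after results are known.

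**Working it through.** **1. The role of each item in the protocol**

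| Item | Arises | Other role in the protocol |
|---|---|---|
| i. Length of GR stay | during treatment | secondary outcome, Table 1 |
| ii. Number of sessions; iii. session duration | during treatment | together they make up amount of physiotherapy, a secondary outcome in Table 1 |
| iv. FIT-HIP components delivered | during treatment, intervention arm only | fidelity measure, Table 3 |

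The same quantities cannot be compared between arms as results of treatment and also be held fixed as confounders of that treatment.

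A path from allocation to items i to iii is plausible on the protocol's own account. The Background links fear of falling to less exercise time in rehabilitation. The Discussion reports some added therapy time in the pilot, described as limited. Neither gives a size.

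**2. The scale used below**

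Sample size gives a POMA difference of 3.8, SD 6.0, two-sided alpha 0.05 and 80% power. The stated 40 per group reproduces: 2 × (1.960 + 0.842)² × 6.0² / 3.8² = 39.1, rounded up to 40. The design effect is 1 + 14 × 0.05 = 1.70, and 40 × 1.70 = 68. Then 68 × 1.10 = 74.8, or 68 / 0.90 = 75.6, against the stated 75. The present point does not touch these figures; 3.8 only sets the scale.

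**3. What adjustment does to the arm coefficient**

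In a linear model with arm and one post-allocation item M:

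adjusted effect = total effect − δ × γ

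Here δ is the difference in M between arms and γ is the within-arm slope of the outcome on M. The documents give neither. The values below are assumptions, with M in SD units. The simulated column comes from a linear model with 400,000 subjects and no clustering.

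| Assumed structure | δ | γ | 3.8 − δγ | Simulated |
|---|---|---|---|---|
| M affects POMA | +0.25 | 2 | 3.30 | 3.30 |
| M affects POMA | +0.50 | 2 | 2.80 | 2.82 |
| M affects POMA | −0.50 | 2 | 4.80 | 4.81 |
| M only shares an unmeasured cause with POMA | +0.50 | −1.5 | 4.55 | 4.57 |
| M only shares an unmeasured cause with POMA | −0.50 | −1.5 | 3.05 | 3.07 |
| Allocation does not change M | 0 | any | 3.80 | 3.77 to 3.79 |

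In the shared-cause rows, better underlying health lowers M by 0.5 SD and raises POMA by 3 points per SD, so γ = −0.5 × 3 = −1.5.

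**4. An example in days of stay**

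Assume frailty adds 10 days and costs 3 POMA points per SD, and that stay has residual SD s. Then γ = −30 / (100 + s²).

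- FIT-HIP shortens stay by 7 days, s = 10: 3.8 − (−7)(−0.15) = 2.75.
- Same, s = 5: 3.8 − 7 × 0.24 = 2.12.
- Same, s = 20: 3.8 − 7 × 0.06 = 3.38.
- FIT-HIP lengthens stay by 7 days, s = 10: 3.8 + 7 × 0.15 = 4.85.

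**5. Item iv**

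Suppose delivery is coded zero in controls. It still varies among intervention patients, so the model can be fitted. The formula applies with δ equal to mean delivery in the intervention arm, which is above zero by design. The arm coefficient becomes an extrapolation to intervention patients who received no FIT-HIP components, and that is not the effect of offering the programme.

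**The case against.** The strongest reply is that the clause only says what can be done. The primary outcomes are defined as plain differences between arms, Data analyses names none of these covariates and promises intention-to-treat, and covariate lists commonly sit in an analysis plan that is not shown. This stands as far as it goes: nothing commits the primary model to these items. But the clause covers the final outcome analyses without restriction and no other section withdraws it. It is a stated use, not an omitted detail.

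A second reply is that recorded therapy is not purely a consequence of FIT-HIP. Under Usual care, each unit has its own agreed therapy intensity, and the Discussion accepts that usual care may differ between units. With 11 units, a chance imbalance is possible. That is fair, and it makes it too strong to call items i to iii mediators and nothing else. It does not make them valid adjusters, because therapy recorded during the trial mixes unit habits with the effect of allocation. The Discussion already assigns such differences to the process evaluation.

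Third, the pilot's limited extra time suggests a small path through the quantity of therapy. That also stands as a reason not to assume a large bias.

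**Conclusion.** Wrong as written. None of the four items can serve as a confounder of the randomised comparison, and using them in the effect models would replace the intention-to-treat estimate with a different quantity. The bias may go in either direction. For items i to iii it is absent only if allocation does not affect them, apart from the trivial case in which the item is unrelated to the outcome within arms and adjustment has no purpose. For item iv the tie to allocation needs no assumption.

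A reader might infer several stronger things that the documents do not support:

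- That the trial will adjust for these items and so has given up intention-to-treat. It has only left the option open.
- That the effect would shrink by a fixed share, such as 3.8 to 2.75 (1.05 / 3.8 = 28%). That needs a shortened stay and a residual SD of 10 days, neither of which is documented; with a lengthened stay the same inputs give 4.85.
- That a particular loss of power follows. No mediated share is given, and adjustment would change the standard error as well as the estimate.
- That item iv is inseparable from arm. Coded zero in controls it is not perfectly collinear; the objection is to what the arm coefficient then means.

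**What to change.** Keep the registration of the four items, which Table 1 and the process evaluation need, and replace only the final clause. The replacement should state two things:

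- The effect models contain arm and pre-specified baseline covariates, with clustering by unit.
- Length of stay, number and duration of sessions, and component delivery are analysed as outcomes, in the process evaluation, or in dose or mediation analyses labelled exploratory and reported separately.

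Any analysis plan should carry the same rule. The cost is one reworded clause, made before the data are analysed. Data collection, patient numbers and the sample size (40 per group, inflated to 75) stay as they are.

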### Blinding

Both the participants and the independent research assistants assessing the outcome measurements are blinded to the group allocation. They are not aware of what usual care is/should be and what the addition of the FIT-HIP intervention is. Healthcare professionals working at the recruitment sites are aware of the allocation status, as the intervention group has been specifically trained to perform the intervention. They are instructed not to inform the participants, family members and the research assistants assessing outcome measures about the allocation status. The main researcher ([name]) was involved in providing the training for the intervention and therefore cannot be blinded in the initial phase of this trial. For data analysis, the database will be processed to blind data to the initial allocation.

To warrant the blinding of participants in the control group (who receive usual care with possibly no specific treatment for or notice of the fear of falling) a dummy intervention is given in both the control and intervention group. The dummy intervention is an information brochure containing information about fear of falling, its consequences, and possibilities for seeking medical attention or help for this problem. This is regarded as an appropriate dummy intervention, as healthcare strategies directed at reducing risk of falling in older adults that use educational interventions alone, have not proven effective [31]. Therefore, we do not expect this information brochure to have a significant effect on the fear of falling.

### Effect evaluation

#### Primary outcome

1. Mean difference in the Tinetti Performance Oriented Mobility Assessment (POMA) score [32, 33] at discharge from GR (or at a maximum of 3 months after admittance to GR), compared between FIT-HIP intervention and usual care. The POMA is a measure of mobility function (gait and balance).

2. Mean difference in the Falls Efficacy Scale International (FES-I) score [34–36] at discharge from GR (or at a maximum of 3 months after admittance to GR), compared between FIT-HIP intervention and usual care. The FES-I is a measure of fear of falling.

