### Sample size

This study tests the null hypothesis that there is no difference in POMA score between the intervention and control group at discharge from GR. The criterion for significance (alpha) was set at 0.050. The test is 2-tailed, which means that an effect in either direction will be interpreted. With a sample size of 40 in both groups, the study will have power of 80% to yield a statistically significant result. Based on our previous research, the minimal clinical relevant difference (mean difference of the POMA at discharge measurement) was set at -3.8, with the common within-group standard deviation at 6.0. The corresponding means are 17.0 vs. 20.8. This effect was selected as the smallest effect that would be important to detect, in the sense that any smaller effect would not be of clinical or substantive significance. It is also assumed that this effect size is reasonable, in the sense that an effect of this magnitude could be anticipated in this field of research.

Compensation for design effect and possible loss to follow-up was taken into account in the choice of sample size. For the design effect (cluster randomisation), the intraclass correlation coefficient (ICC) for the outcome measure POMA is expected to be 0.05 because of clustering of data and because there may be inequality of the numbers within clusters. For the possible loss to follow-up, specifically death in the 3-month rehabilitation phase is not expected be ≥10%. Instead of the 40 patients calculated with the power analysis, we will include 75 patients per group.

As 11 post-acute GR units were interested in participating, we decided to include one additional intervention post-acute GR unit, in case of unsuspected drop-out of one intervention location. Thus, we aim to include a total of 165 participants.

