### Data analyses

Differences between the intervention and control group in characteristics of participants at baseline will be tested with chi-square tests for categorical variables, Mann-Whitney *U*-test for continuous variables with skewed distributions, and one-way ANOVA for normally distributed continuous variables. Given the hierarchical data structure, multilevel analyses will be used for continuous outcomes, and logistic Generalized Estimated Equation (GEE) analyses for dichotomous outcomes. Logistic GEE is preferred to logistic multilevel analyses because of the instability of the latter. Analyses will be based on an intention-to-treat principle and the level of significance will be set at *p* < 0.05. Missing data will be handled as missing (no imputation). Multilevel analyses will be performed with MLwiN. All other analyses will be performed with IBM SPSS statistics.

With regard to the qualitative data (assessed for the process evaluation), these will be analysed by means of coding techniques based on transcriptions of the qualitative interviews. In the economic evaluation, group averages will be compared using unequal-variance t-tests, according to the intention-to-treat principle. Costs will be compared to QALYs using net-benefit analysis. Multiple imputation will be used to account for missing values. Sensitivity analysis will be performed on the time horizon (base case 6 months vs. 12 months) and the utility measure (base case Dutch EQ-5D tariff vs. visual analogue scale for health).

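### Unit staff know their arm before patients are recruited, yet no baseline adjustment is named, the only adjusters named arise after allocation, and baseline tests ignore clustering

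*Protocol article*

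**What the plan says.** All references are to the protocol article.

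- **Primary outcome.** The first primary outcome is "Mean difference in the Tinetti Performance Oriented Mobility Assessment (POMA) score" at discharge from rehabilitation, or at most 3 months after admission, compared between arms. The second is the same contrast for FES-I.
- **Randomisation (and allocation).** Six units go to the intervention and five to control. Patients are screened on admission and enrolled "in order of succession in which patients are admitted to GR, eligible, and willing to participate", up to 15 per unit.
- **The FIT-HIP intervention; Blinding.** Intervention physiotherapists are trained before participants are recruited, and "Healthcare professionals working at the recruitment sites are aware of the allocation status". Participants and outcome assessors are stated to be blinded.
- **Data analyses.** Continuous outcomes get multilevel models because the data are hierarchical, and no covariate is named. For baseline, "Differences between the intervention and control group in characteristics of participants at baseline will be tested with chi-square tests for categorical variables", with Mann-Whitney tests for skewed and one-way ANOVA for normally distributed variables. Missing data in the effect analysis are not imputed.
- **Duration of the FIT-HIP intervention.** Length of stay, number and duration of therapy sessions, and (intervention arm only) the components performed may be used as confounders in the final outcome analyses.

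**The concern.** Randomising units does not by itself make the recruited patients comparable when they enter after staff know the arm. Willingness to take part, and a self-reported answer to one fear question, decide who is enrolled. With 11 units, chance imbalance is also to be expected. A contrast of discharge scores without a baseline term carries any such difference into the result.

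The adjustment that the article does mention does not address this. Length of stay and amount of therapy follow allocation and may be changed by the intervention, so conditioning on them can remove part of the effect or introduce bias. Components performed are recorded only in the intervention arm, so they cannot act as a confounder of the comparison between arms.

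The baseline tests treat patients as independent, although the same section uses multilevel models for the outcomes for exactly that reason. Their p-values are therefore too small on average, and they cannot separate chance imbalance from recruitment bias.

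**Working it through.** **1. The plan's own figure.** The inputs under Sample size are a two-sided alpha of 0.05, a target of 80% power (reached, it says, with 40 per arm), a POMA effect of 3.8 points ("mean difference of the POMA at discharge measurement) was set at -3.8"), SD 6.0, ICC 0.05, and loss below 10%.

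- n per group = 2 × (1.96 + 0.84)² × 6.0² / 3.8², which rounds up to 40. Power at 40 per group is 80.9% (normal) or 79.9% (t test).
- Design effect = 1 + (15 − 1) × 0.05 = 1.70, and 40 × 1.70 = 68.
- Loss: 68 / 0.90 = 75.6, so 76; or 68 × 1.10 = 74.8, so 75.

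The stated 75 per group reproduces to within one patient.

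**2. Error rate of the baseline tests.** With no true difference, a patient-level test at nominal 5% rejects with probability 2 × [1 − Φ(1.96 / √DE)], where DE = 1 + (m − 1) × ICC. The documents give an ICC only for the POMA outcome, so the ICC of baseline variables is an assumption, shown as a range.

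| ICC | DE, m = 13.5 | Rejects | DE, m = 15 | Rejects |
|---|---|---|---|---|
| 0.01 | 1.125 | 6.5% | 1.14 | 6.6% |
| 0.05 | 1.625 | 12.4% | 1.70 | 13.3% |
| 0.10 | 2.25 | 19.1% | 2.40 | 20.6% |

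Simulation of 6 vs 5 units of 15 patients gave 6.4%, 13.2% and 20.7%.

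**3. Bias from a baseline imbalance.** If recruitment shifts baseline POMA by D standard deviations in one arm, and the baseline-discharge correlation is r, the unadjusted contrast is biased by about r × D × 6.0 points. D and r are both assumed.

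- D = 0.25: r = 0.3 gives 0.3 × 0.25 × 6.0 = 0.45 points and r = 0.7 gives 1.05 points, which is 12% to 28% of the 3.8-point target.
- D = 0.5: 0.9 to 2.1 points.

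In simulation the unadjusted bias was close to these values. Adjusting for the baseline score reduced it to about zero, and at r = 0.5 the empirical standard error fell from about 1.25 to 1.07.

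**4. Precision and power.** SE = 6.0 × √[(1 − r²) × DE × (1/n₁ + 1/n₂)]. Take 13.5 analysed per unit (15 less 10%) and ICC 0.05, so DE = 1 + 12.5 × 0.05 = 1.625. This assumes that unit-level variance falls by the same factor 1 − r².

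- 6 vs 5 units, unadjusted: n = 81 and 67.5, SE = 1.26, 3.8 / 1.26 = 3.01.
- 5 vs 5 units (one intervention unit lost), unadjusted: n = 67.5 and 67.5, SE = 1.32, 3.8 / 1.32 = 2.89.

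The t column uses the number of units minus 2 degrees of freedom (9 and 8).

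| r (assumed) | 6 vs 5: normal | 6 vs 5: t | 5 vs 5: normal | 5 vs 5: t |
|---|---|---|---|---|
| 0 (unadjusted) | 85% | 77% | 82% | 72% |
| 0.3 | 88% | 80% | 86% | 76% |
| 0.5 | 94% | 87% | 92% | 83% |
| 0.6 | 96% | 92% | 95% | 88% |

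**The case against.** **The article is silent on covariates; it does not exclude them.** A baseline-adjusted multilevel model estimates the same mean difference at discharge, and a covariate list is something a condensed article may leave to the analysis plan. This stands: silence alone would be no finding. What remains is that the article does speak about adjustment, and names only variables that arise after allocation. A reader might infer that the plan commits to a raw, unadjusted contrast. The text does not say so, and the multilevel model does handle clustering.

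**Nothing needs restoring.** A reader might infer that the trial is underpowered without adjustment. The stated sample size reproduces, and on its own normal-theory basis power is 82-85%. The 72-77% appears only with few-cluster degrees of freedom; it also takes the full 10% loss and, at its lower end, a lost unit. The correlation is not documented.

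**The baseline tests have no stated consequence.** A reader might infer that they choose the covariates. No such rule is given, so false flags affect the p-values in the baseline table, not the primary result.

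**Recruitment bias is possible, not shown.** Enrolment follows the order of admission, and participants are stated to be blinded, which limits selection. The article does not say who asks the fear question or takes consent, so it cannot be said that allocation-aware staff do so. What stands against this objection is that screening takes place in units whose staff know the arm, and that chance imbalance with 11 units needs no selection at all.

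**Conclusion.** The point holds as a recommended improvement. Two stated choices are poorly suited to the design: offering post-allocation variables as confounders, and testing baseline balance as if patients were independent. The second has a true error rate of about 6.5% to 21% over assumed ICCs of 0.01 to 0.10. In addition, pre-specified baseline adjustment is a better method than the discharge contrast with no named baseline term. Under an assumed 0.25 SD imbalance it would remove roughly 0.4 to 1.0 POMA points of bias. Its gain in power is 4 to 16 percentage points on few-cluster degrees of freedom for r of 0.3 to 0.6, starting from power that is already adequate on the plan's own basis.

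These sizes rest on assumed values for the correlation, the imbalance and the ICC of baseline variables. They also assume that POMA and FES-I are measured at baseline; the article as shown lists no time points for them. Adjustment deals only with measured factors.

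**What to change.** 1. Pre-specify that the primary multilevel model regresses the discharge score on arm, the baseline value of the same scale and a short fixed list of baseline factors, with a random effect for unit and a small-sample correction. If POMA or FES-I is not taken at baseline, use the Barthel index, Functional Ambulation Categories and walking speed, all scheduled at baseline in Table 1.
2. State that length of stay, number and duration of sessions, and components performed stay out of the primary model. They can serve the process evaluation.
3. Replace the baseline significance tests with descriptive tables by arm.

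The cost is a change of analysis wording, using data already planned. There is one small downside: with no imputation, a patient with a missing baseline covariate drops out of the model, so the plan should say how such values are handled. Selection on unmeasured factors is not cured by adjustment. The protocol should therefore also state who screens and takes consent, and whether that person knows the unit's arm.
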